**Discussion:**

This project is the first comprehensive research project to assess whether social support influences adherence to an activity advice outside the clinical setting without supervision of a healthcare provider. Where evidence of influence on social support is lacking, findings may have implications for the management of patients with low back pain. In addition, findings may enable physiotherapists to predict in which patients with low back pain an activity advice with social support makes sense.

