Social support is known as one of the most important factors predicting physical health (Oraison & Kennedy, 2019). While various definitions of social support have been proposed in the literature, most research recognizes social support as the help perceived (i.e., emotional, practical) from others in social networks (Oraison & Kennedy, 2019). In this study, the influence of social support on adherence to an activity advice will be investigated. For the purpose of this study, it is hypothesized that organizing social support by a partner or friend will be a potential treatment option to increase adherence to a physical activity advice. This intervention fits the context of the new health definition where health is defined ‘as the ability to adapt and to self‐manage, in the face of social, physical, and emotional challenges’ (Huber, 2014).

There is evidence indicating that illness beliefs predict health behaviour and activity limitations in low back pain. To minimize negative influence of maladaptive illness beliefs on adherence to a physical activity advice in patients with low back pain (Siemonsma et al., 2013), in this randomized controlled trial, treatment of illness beliefs is added.

Because evidence on clinical barriers is conflicting and limited, influence of confounding factors, such as age, gender, education level, pain and disability, comorbidity, and patient's intention and attitude to physical activity will also be studied. It is hypothesised these factors influence adherence.

The primary objective of this study is to investigate if patients with low back pain randomised to receive social support adhere better to an activity advice than patients randomised to the control group.

Secondary objectives are; whether patients with low back pain perceiving social support during physiotherapy treatment adhere better to an activity advice compared to patients with low back pain without perceiving social support during treatment, and, if age, gender, education level, pain and disability, treatment of illness beliefs, comorbidity and attitude and intention to physical activity influences a patient's adherence to an activity advice.

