### Interventions

2.2

During treatment, according to the Dutch guideline for low back pain, patients in the intervention and control group are asked to walk and/or cycle outdoors in accordance with the DSHPA (Hildebrandt et al., 2007).

In the intervention group illness beliefs according to Leventhal's Common‐Sense Model of self‐regulation will be discussed with the patient and the partner or friend (Siemonsma et al., 2013). During two half‐hour consultations maladaptive beliefs and feelings about low back pain are mapped in a standardized dialogue, maladaptive beliefs are challenged, evidence‐based beliefs as an alternative are formulated, and the utility is tested to become physically active according the DSHPA (Siemonsma et al., 2013). Organization of social support by a partner or friend is added. In a standardized discussion the partner or friend of the patient will be advised to organize social support for executing the activity advice.

In the control group only the illness beliefs according to Leventhal's Common‐Sense Model of self‐regulation will be discussed with the patient and the partner or friend (Siemonsma et al., 2013).

Only when requested by the patient the intervention will be discontinued.

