#### Secondary outcomes

2.3.3

The Social Support Scale is a study specific questionnaire and assesses the rate of social support perceived by the patient and performed by the partner (Appendix 1). This questionnaire must be filled in by the patient and the partner after the investigation period and has dichotomous outcomes.

The Dutch Illness Perceptions Questionnaire Short‐form (DIPQ‐S) assesses patients' and partner/friends' illness beliefs (Appendix 1). Eight items about illness beliefs are scored on a 0–10‐point scale, one item is an open question. The questionnaire has good reliability and validity (Broadbent et al., 2006; de Raaij, Schröder, Maissan, Pool & Wittink, 2012; Leysen et al., 2015). The DIPQ‐S will be filled in at baseline, 1, 6 and 12 weeks follow up by the patient and at baseline, 1 and 12 weeks follow up by the partner or friend.

The module attitude and intention (MAI) of The Knowledge, Attitude, Self‐efficacy and Self‐regulation, Exercise and Social Support for Sports and Exercise Questionnaire will be used to assess attitude and intention to be physically active (Wink, van Woerkom & Renes, 2006). Attitude (6 items) can be scored from 6 (most negative) to 42 points (most positive), while intention (3 items) can be scored from 3 (most negative) to 21 points (most positive). Validity of this questionnaire is unknown, but it was used in the FLASH! Campaign from the Dutch Institute for Sport and Exercise in 2003–2006 (Appendix 1). This questionnaire will be filled in at baseline and after 12 weeks by the patient and partner or friend.

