### Statistical methods

2.9

To analyse the data SPSS version 25.0 (IBM SPSS, Chicago, IL, USA) will be used. For demographic data descriptive statistics will be used and normality assumptions for the variables will be checked. An intention‐to‐treat analysis will be used for the main outcome. To correspond to the primary aim of the study, outcomes of the Activ8 will be dichotomized into adherent and not adherent patients in the intervention and control group. The Chi^2^ test will be used to investigate if there is a significant difference in the proportion of adherent patients to the activity advice between the intervention and control group after one, six and 12 weeks, and if there is a significant difference in the proportion of adherent patients between patients who experienced social support or not on the social support scale after 12 weeks. A Time Series Analysis will be used to present changes over time in perceived illness beliefs of patients and partner/friend. To understand whether illness beliefs influence adherence, Pearson's r between outcomes of the IPQ‐S at baseline and after 12 weeks and (non)adherence measured by the Active8, will be calculated, and linear regression will be used for modelling the relationship between these outcomes. To assess the correlation between attitude and intention to physical activity (MAI) and adherence at 12 weeks, Pearson's will be calculated, and linear regression will be used for modelling the relationship between these outcomes. Influence of age, gender, education level, comorbidity (CIRS), pain (VAS) and disability (QBPDS) on adherence, will be estimated by multiple regression analyses. A *p* value of <0.05 will be considered statistically significant.

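### Two secondary objectives and one promised conclusion do not match the analyses described: perceived support, treatment of illness beliefs, and who should get social support

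*Protocol article*

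**What the plan says.** **Objectives.** The Introduction lists two secondary objectives. The first asks "whether patients with low back pain perceiving social support during physiotherapy treatment adhere better to an activity advice compared to patients" who do not perceive it. The second asks "if age, gender, education level, pain and disability, treatment of illness beliefs, comorbidity and attitude and intention to physical activity influences" adherence. The same section calls most of these factors confounding and hypothesises that they affect adherence.

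**Perceived support.** Under Secondary outcomes (2.3.3), the Social Support Scale "must be filled in by the patient and the partner after the investigation period and has dichotomous outcomes". Statistical methods (2.9) then tests adherence by Chi-square "between patients who experienced social support or not on the social support scale after 12 weeks". No covariate is named for this comparison, and arm is not mentioned.

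**Illness beliefs.** Interventions (2.2) provides the illness-belief consultations in the intervention arm and adds the organising of social support. For the other arm it reads "In the control group only the illness beliefs according to" the same model are discussed. Section 2.9 describes change in belief scores over time and relates the scores at baseline and week 12 to adherence by Pearson's r and linear regression.

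**Who should get support.** The abstract says that "findings may enable physiotherapists to predict in which patients with low back pain an activity advice with social support makes sense", and the Discussion (section 3) repeats this. The multiple regression in 2.9 lists three demographic factors, comorbidity, pain and disability as predictors of adherence. Section 2.7 separately hypothesises that patients with a higher BMI or more than three episodes respond less to the interventions, and stratifies on both.

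**The concern.** In each case the data analysis described answers a different question from the one posed.

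- Perceived support is not randomised. A motivated patient is plausibly more likely both to be active and to report having been supported. Because the scale is completed after the investigation period, patients also know by then how active they were. Arm, motivation, recall and any real effect of support are all mixed in one two-by-two table.
- A treatment that everyone receives offers no contrast, so nothing can be learned about its influence on adherence.
- Factors that predict adherence are not the same as factors that predict benefit from support. The second needs a comparison of the arm effect across levels of the factor.

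At stake is a report that presents a confounded difference as an effect, leaves one objective unanswered, and gives clinicians a patient-selection message that no analysis supports.

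**Working it through.** The article gives no figure for these objectives and no adherence rates. Inputs taken from it are 142 evaluable patients and 80% power (2.5) and a significance level of 0.05 (2.9). Equal arms of 71 and two-sided testing are assumed. All rates below are assumptions, chosen to show a range.

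**1. Perceived support with no true effect.** Let half the patients have some baseline trait. Let s0 and s1 be the probability of reporting support without and with the trait, and a0 and a1 the probability of adhering. Given the trait, support and adherence are independent. Then

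- P(adherent | support) = (s0·a0 + s1·a1) / (s0 + s1)
- P(adherent | no support) = [(1−s0)·a0 + (1−s1)·a1] / [(1−s0) + (1−s1)]

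Example with s = 0.30, 0.70 and a = 0.20, 0.60: (0.06 + 0.42)/1.00 = 0.48 against (0.14 + 0.18)/1.00 = 0.32, a spurious 16 points. With 71 patients per group and 40% adherent overall, the critical difference is 1.96 × √(2 × 0.40 × 0.60/71) = 1.96 × 0.0822 = 0.161. The standard error of the observed difference is √[(0.48 × 0.52 + 0.32 × 0.68)/71] = 0.081. The chance of significance in favour of support is therefore P(Z > (0.161 − 0.160)/0.081), about 49%.

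| Support without / with trait | Adherence without / with trait | Spurious difference | Chance of significance in favour of support |
|---|---|---|---|
| 40% / 60% | 30% / 50% | 4 points | 7% |
| 30% / 70% | 30% / 50% | 8 points | 16% |
| 30% / 70% | 20% / 60% | 16 points | 49% |
| 20% / 80% | 20% / 60% | 24 points | 84% |

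Without confounding the last column would be 2.5%.

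**2. Treatment of illness beliefs.** No arithmetic is needed. The Introduction makes the treatment an explanatory factor, and section 2.2 gives it to both arms. The factor is constant, so no coefficient for it can be estimated at any sample size. What section 2.9 analyses is the belief score, which varies between patients, and not its treatment.

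**3. Who benefits.** A difference between two subgroup effects, with the sample split in half, has a standard error twice that of the main effect. Example with control adherence 30%: the difference detectable at 80% power is 23 points.

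- Main-effect standard error: √[(0.30 × 0.70 + 0.53 × 0.47)/71] = 0.080.
- Interaction standard error: √[2 × (0.30 × 0.70 + 0.53 × 0.47)/35.5] = 0.161.
- Power for a 23-point interaction: P(Z > 1.96 − 0.23/0.161) = P(Z > 0.53), about 30%.
- Interaction detectable at 80% power: 2.80 × 0.161 = 0.45.

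For control adherence from 20% to 50%, the detectable main effect is about 22 to 23 points, interaction power stays near 30%, and the detectable interaction is about 42 to 46 points.

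**The case against.** A reader might infer that three stated secondary aims cannot be answered. The documents do not support that.

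- The perceived-support objective is worded as a comparison of groups, and a Chi-square does answer it as an association. Neither the objective nor section 2.9 says that a causal effect will be reported. What stands is that nothing labels the result as an association, while the Introduction frames the study as one of the influence of support on adherence.
- It would go too far to say that the illness-belief objective has no data behind it. Patients complete the belief questionnaire at baseline and at 1, 6 and 12 weeks, section 2.9 analyses the scores, and the Discussion states an interest in whether change in beliefs affects adherence. What stands is a faulty phrase in the objective. The abstract describes the control as usual care alone, which could suggest a contrast, but section 2.2 is explicit that both arms have their beliefs discussed. Those two descriptions need reconciling.
- Predicting who suits support is a hoped-for use of the findings and not a listed objective. A reader might also infer that the regression contains main effects only. The article does not give the full model, and an analysis plan that is not shown may include arm or interactions. What stands is that the promised conclusion does not follow from the analysis described.

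The magnitudes depend on invented rates. They show direction and plausible range, and are not an estimate for this trial.

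**Conclusion.** The mismatch is real in all three places, with different force.

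- Treatment of illness beliefs is the firmest. The objective and the design contradict each other, and no assumption is involved.
- The perceived-support test is interpretable only as an unadjusted association. If a baseline trait drives both support and adherence, the spurious difference is about 4 to 24 points at 142 patients, with a 7% to 84% chance of a significant result in favour of support. This rests entirely on the assumed rates.
- The prediction statement goes beyond the regression described, which identifies who adheres. It also leaves out the two factors that section 2.7 expects to modify response. Stratifying on them balances the arms but does not test modification.

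The primary randomised comparison, the design and the sample size are unaffected. The sponsor should correct this before analysis, mainly through wording.

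**What to change.** 1. **Perceived support.** Replace the Chi-square with a logistic regression of week-12 adherence on perceived support, adjusted for arm and a small prespecified set of baseline factors such as attitude, intention, pain and disability. Report it with a confidence interval as an exploratory association. Adjustment does not remove recall or reverse causation, and the text should say so. The covariate set must stay small. If 20% to 50% of 142 patients adhere (assumed), there are 28 to 71 adherent patients. With the six parameters named here (support, arm and four factors) that is about 5 to 12 per parameter.
2. **Illness beliefs.** Reword the objective as the association of illness beliefs, and of their change on the DIPQ-S, with adherence. Section 2.9 already does most of this. Reconcile the abstract with section 2.2 on what the control arm receives.
3. **Who benefits.** Either withdraw the prediction statement from the abstract and Discussion, or add arm and a few arm-by-factor terms that include BMI and number of episodes. Label these exploratory, give confidence intervals and state the low power.

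All variables are already collected, so the cost is some redrafting, a few model terms and more modest claims.

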### Timeline

2.4

Eligible patients will be recruited for the study together with their partner or friend by the assessing physiotherapist and will receive information about the study. If patients and partners or friends decide after 1 week of consideration they want to be included in the study, written informed consent will be asked to the patient and partner or friend and base‐line assessment of the patient and partner or friend will be performed (Appendix 1). After base‐line assessment the assessor explains to the patient that further treatment will be performed by an IGP or CGP. The patient will be contacted within 2 days for an appointment with either the IGP or CGP. The patient and partner/friend will be instructed to come both to the next two appointments. The assessor contacts the randomization centre. The randomisation centre allocates the patient for IGP or CGP and informs the assessor. The assessor instructs the IGP or CGP to make the next appointments with the patient and their partner/friend.

After the first intervention on illness beliefs with or without organizing social support, treatment will be applied according to the Dutch guideline for low back pain (Staal et al., 2013). In both groups' patients are instructed in executing the activity advice in accordance with the DSHPA and to wear a move monitor for 1 week (Hildebrandt et al., 2007). In the group in which the social support is given, the partner/friend will be asked to make a week schedule of times, activities, and contact‐control moments for the coming months.

At the end of the week the activity monitors will be returned, and questionnaires will be filled out. The second intervention on illness beliefs with or without organizing social support takes place and treatment will be applied according to the Dutch guideline for low back pain (Staal et al., 2013). After six‐ and 12‐weeks patients will be invited by the assessors to wear the Active8 for one week and to fill in the questionnaires. During the study period the IGP contacts the partner/friend in week 6 and 10 to evaluate whether social support was given. At the last appointment also the partner or friend will be invited and asked to fill in questionnaires. Enrolment of the study is shown in the flow diagram (Figure 1).

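### The 12-week illness-belief score is measured with the outcome and cannot show influence on adherence; the better-timed week-6 score is not named in that analysis

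*Protocol article*

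**What the plan says.** Section 2.9 of the protocol article gives the purpose of this analysis as learning whether illness beliefs influence adherence. It names the belief scores to be correlated with adherence: "at baseline and after 12 weeks and (non)adherence measured by the Active8, will be calculated". Linear regression on the same outcomes follows.

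Section 2.3.3 (Secondary outcomes) shows that more scores are collected. The DIPQ-S "will be filled in at baseline, 1, 6 and 12 weeks follow up by the patient".

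Section 2.2 (Interventions) says that illness beliefs are discussed in both arms. It describes two half-hour consultations in which "maladaptive beliefs are challenged, evidence"-based alternatives are formulated.

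Section 2.4 (Timeline) gives the order of events:
- Consent, baseline assessment and allocation come first.
- Then: "After the first intervention on illness beliefs with or without organizing social support, treatment will be applied according to the Dutch guideline". The first monitored week starts here.
- The week-1 follow-up is next: "At the end of the week the activity monitors will be returned, and questionnaires will be filled out".
- Only after this does the text place the last belief session: "The second intervention on illness beliefs with or without organizing social support takes place".
- After six and after 12 "weeks patients will be invited by the assessors to wear the Active8 for one week and to fill in the questionnaires".

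The only other planned use of the repeated belief scores is a Time Series Analysis in section 2.9. It presents change over time and is not linked to adherence.

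**The concern.** The stated purpose is directional: beliefs acting on behaviour. Of the two scores chosen, one comes before the treatment of beliefs and the other is taken together with the outcome.

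A patient who managed to walk or cycle for 12 weeks may, for that reason, feel more in control of the back pain and score accordingly. A patient who did not manage may score worse. Either would produce a 12-week correlation without beliefs having any effect on adherence. Under the heading of influence, that correlation would be read as support for treating beliefs in order to raise adherence. Section 1 makes the influence of treating illness beliefs on adherence part of the secondary objectives, and the Discussion is interested in whether change in beliefs affects adherence. The reading therefore matters, although the primary comparison does not depend on it.

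**Working it through.** The plan gives no figure to reproduce on this point. The check compares the schedule with the analysis and then illustrates the size of the problem.

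**Step 1. Place each patient DIPQ-S score in the sequence (sections 2.3.3 and 2.4).**

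| Score | Relative to belief sessions | Relative to 12-week adherence | Named in the belief–adherence analysis |
|---|---|---|---|
| Baseline | before both | before | yes |
| Week 1 | described between first and second | before | no |
| Week 6 | after both | before | no |
| Week 12 | after both | same assessment | yes |

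Week 6 is the only score that follows both sessions and precedes the 12-week outcome.

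**Step 2. Which week's adherence?** The sentence on beliefs does not say. Week 12 is inferred from section 2.5, which sizes the trial on adherence after 12 weeks. If adherence at week 1 or 6 were meant, the 12-week score would come after its outcome, and the problem would be larger.

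**Step 3. How often would a purely reverse association be significant?** Inputs: n = 142 (section 2.5); alpha 0.05 (section 2.9), taken as two-sided; r is assumed, since the documents give no value. By Fisher's z, power ≈ Φ(atanh(r)·√(n − 3) − 1.96), with √139 = 11.790.
- r = 0.2: 0.2027 × 11.790 = 2.390; Φ(0.430) = 0.67
- r = 0.3: 0.3095 × 11.790 = 3.649; Φ(1.689) = 0.95
- r = 0.4: 0.4236 × 11.790 = 4.995; Φ(3.035) = 0.999
- r = 0: 0.05, by construction

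**Step 4. Would the week-6 score repair this?** Simulation with 6,000 trials per row. Assumptions not in the documents: 40% adherent at each visit; no effect of beliefs on adherence; correlation 0.5 between belief scores at different visits before any shift; latent correlation of adherence between visits 0.5 or 0.7; adherence shifts the same-visit belief score by the amount shown. The models are linear, as in the plan. Entries are the proportion of trials in which the belief term is significant at 5%.

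| Shift (SD) | Latent correlation | 12-week score alone | Week-6 score + baseline score + arm | The same + adherence at weeks 1 and 6 |
|---|---|---|---|---|
| 0 | 0.5 / 0.7 | 4% / 5% | 5% / 4% | 5% / 5% |
| 0.20 | 0.5 / 0.7 | 21% / 22% | 7% / 10% | 5% / 5% |
| 0.41 | 0.5 / 0.7 | 66% / 66% | 14% / 25% | 5% / 6% |
| 0.66 | 0.5 / 0.7 | 97% / 96% | 28% / 54% | 5% / 5% |

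The week-6 score is better timed but not sufficient alone, because adherence persists and may already have shaped week-6 beliefs. In this model, adding earlier adherence brings the false-positive rate back to about 5%.

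**The case against.** **Baseline beliefs are a legitimate predictor.** This stands. They cannot be caused by later adherence, and they fit the Discussion's wish to predict at presentation for whom the advice makes sense. A week-6 score cannot serve that purpose. A reader might infer that the objective goes unanswered. The documents do not support that: the baseline analysis answers part of it, namely whether untreated beliefs predict adherence.

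**The week-6 score is not discarded.** A reader might infer from section 2.9 that it is never used. It presumably enters the Time Series Analysis. What holds is narrower: it is not named where beliefs are related to adherence.

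**Attitude and intention (MAI).** It is tempting to extend the point to this questionnaire, of which section 2.3.3 says "This questionnaire will be filled in at baseline and after 12 weeks by the patient and partner or friend". The analysis sentence speaks only of correlation, and its 12-week label can be read as belonging to adherence, so the MAI visit is simply left open. A condensed article may leave that to the full plan, so it is no fault here.

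**The significance rates assume what they show.** This is largely fair. They say how readily a reverse association would be detected if it existed, not that it exists. With no reverse effect the rate is 5%.

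**It is one secondary, explanatory analysis.** Correct, and the Discussion itself is modest about belief change. That limits the weight of the point. It does not make a concurrent correlation evidence of influence.

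**Conclusion.** The point holds in a limited form. The 12-week DIPQ-S correlation cannot separate beliefs acting on adherence from adherence acting on beliefs, and it is planned under a purpose worded as influence. A score with better timing is already collected but not named in that analysis.

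This rests on the sequence in section 2.4 and on the inference that 12-week adherence is the outcome. The rates of 67%, 95% and over 99% depend on assumed reverse correlations of 0.2, 0.3 and 0.4, and they illustrate rather than predict. It would also go too far to conclude that a week-6 analysis would establish influence: with persistent adherence and no belief effect, a week-6 model without earlier adherence was falsely significant in 14% to 54% of simulated trials at shifts of 0.41 and 0.66 SD. The plan should be changed here, but the primary comparison between arms is untouched.

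**What to change.** In section 2.9:
1. Keep the baseline DIPQ-S analysis, described as prediction of adherence from beliefs before treatment.
2. Add a model of 12-week adherence on the week-6 DIPQ-S, adjusted for baseline DIPQ-S, arm and Activ8 adherence at weeks 1 and 6.
3. Report the 12-week DIPQ-S correlation as a concurrent association, with no statement of influence.
4. State that adherence at week 12 is the outcome in these analyses.

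There is no cost in data collection, since sections 2.3.2 and 2.3.3 already provide every variable. Patients without week-6 data leave this secondary analysis unless their values are imputed, and missing week-1 monitor data have the same effect. The lagged model reduces confounding but does not remove it, so its result should still be worded with care.

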#### Primary outcome

2.3.2

Adherence to the activity advice according to the DSHPA is the primary outcome measure and will be measured by a 3D accelerometer (Activ8, 2M engineering, Valkenswaard, the Netherlands). During the assessment periods at one, six‐ and 12‐week patients are instructed to wear the Activ8 every day during one week. The number of days per week patients have walked or cycled according to the advice will be counted. Cut‐off for adherence will be set at a minimum of 5 times per week of at least 30 min walking and/or cycling. The Activ8 system is a valid instrument to quantify body postures and motions (Fanchamps et al., 2018). For this study only the walking and cycling activities recorded by the monitor will be used for analyses.

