## DISCUSSION

3

This project is the first comprehensive research project to assess whether social support influences adherence to an activity advice outside the clinical setting without supervision of a healthcare provider. Unique in this study is that intervening on illness beliefs will be provided to patient and partner to minimize the influence of maladaptive illness beliefs on adherence. Literature mentions that intervention on illness beliefs changes outcomes of the DIPQS, however, responsiveness of the questionnaire is lacking (Broadbent et al., 2015). Despite this, it is of interest if a tendence of change over time may occur and influence outcomes of adherence.

Where evidence on clinical barriers is conflicting and limited, complementary, influence of age, gender, education level, comorbidity, attitude and intention to physical activity and perceived pain and disability on adherence will be investigated. Findings have implications for the management of patients with low back pain, enabling prediction as to which low back pain patient giving an activity advice with social support makes sense.

It is important to note the variation in how concepts of (non)adherence are operationalized in existing literature resulting in variable outcomes (Essery et al., 2017; van Koppen et al., 2020). For robust outcomes in this study an accurate definition of the activity advice is applied, mentioning frequency and duration, and outcomes of adherence are dichotomous, measured with a validated move monitor.

Strengths of the study are the concealed allocation and the randomization. To reduce the presence of observer bias, measurements will not be performed by the treating physiotherapist.

Treatment of both groups in one physiotherapy practice is preferred to overcome selection bias. This implicates that despite the standardized protocol and the strict requirements to ensure blinding, it is possible that patients and treating physiotherapist exchange information about the interventions. This may influence outcomes and is therefore a limitation of the study.

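### Pearson's r and linear regression are named for a dichotomous adherence outcome, and a time-series analysis for illness beliefs measured only three or four times

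*Protocol article*

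**What the plan says.** **Scale of adherence.** Section 2.3.2 first produces a count: "The number of days per week patients have walked or cycled according to the advice will be counted". It then sets a cut-off for adherence, a "minimum of 5 times per week of at least 30 min walking and/or cycling". Section 2.9 says that "outcomes of the Activ8 will be dichotomized into adherent and not adherent patients in the intervention and control group". The Discussion presents this as a strength: "outcomes of adherence are dichotomous, measured with a validated move monitor".

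**Methods for predictors of adherence (Section 2.9).**
- IPQ-S at baseline and 12 weeks against (non)adherence: Pearson's r, and "linear regression will be used for modelling the relationship between these outcomes".
- MAI against adherence at 12 weeks: the same two methods, in the same words.
- Age, gender, education, CIRS, VAS and QBPDS: multiple regression, with no type named.

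**Method for change in illness beliefs.** "A Time Series Analysis will be used to present changes over time in perceived illness beliefs", for patients and partners. Section 2.3.3 gives the schedule: the questionnaire "will be filled in at baseline, 1, 6 and 12 weeks follow up by the patient", and partners complete it at baseline, 1 and 12 weeks.

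The article names no logistic model and no repeated-measures model.

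**The concern.** Linear regression is built for a continuous outcome. On a 0/1 outcome it becomes a linear probability model: the error variance changes with the fitted value, and a fitted probability can fall below 0 or above 1. Pearson's r becomes the point-biserial correlation, whose largest attainable value depends on how many patients adhere. The same strength of association would therefore give different values of r in settings with different adherence rates. The Discussion wants the findings to show in which patients the advice with social support makes sense, and attitude/intention is among the factors listed there. Predicted probabilities are where the linear model is weakest.

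Time-series methods model autocorrelation in one long series, usually equally spaced. The illness-belief data are the opposite: a very short, unequally spaced record on each of many people. A reader following the text literally would have no usable model for them.

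**Working it through.** The plan gives no figure on this point to reproduce. The check sets variable type against method, then sizes the consequence.

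**1. Is adherence binary where these methods are applied?** Sections 2.3.2 and 2.9 and the Discussion all make it binary. For IPQ-S, Section 2.9 itself writes (non)adherence. The stated question is whether beliefs influence adherence, so adherence is the dependent variable.

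**2. Ceiling on r.** Assume adherence is a perfect threshold on a normally distributed predictor, with share p adherent. Then r_max = φ(z_p) / √(p(1−p)).
- p = 0.5: 0.3989 / 0.5 = 0.80
- p = 0.2: 0.2800 / 0.4 = 0.70
- p = 0.1: 0.1755 / 0.3 = 0.58

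**3. Linear against logistic regression.** Simulation with N = 142 (Section 2.5), one standardised normal predictor and 1,000 trials per setting. The documents give no adherence rates or effect sizes, so these are assumed: adherence of 20%, 35% or 50% at the predictor mean, and log-odds slopes of 0.5 or 1.0 per SD.

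| Adherence at mean | Slope | Trials with any fitted value outside 0-1 | Mean share of fitted values outside 0-1 | Power, linear / logistic |
|---|---|---|---|---|
| 20% | 0.5 | 47% | 1.4% | 0.626 / 0.619 |
| 35% | 0.5 | 22% | 0.3% | 0.779 / 0.769 |
| 50% | 0.5 | 10% | 0.1% | 0.810 / 0.805 |
| 20% | 1.0 | 98% | 6.5% | 0.996 / 0.995 |
| 35% | 1.0 | 91% | 3.2% | 0.998 / 0.998 |
| 50% | 1.0 | 83% | 2.2% | 0.999 / 0.999 |

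Under the null (30% adherent, 3,000 trials), type I error was 0.050 for linear and 0.049 for logistic regression. A further simulation with one, two or six predictors, and adherence from about 8% to 50%, kept the linear model's type I error between about 0.04 and 0.06.

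**4. Illness-belief series.**
- Patients: weeks 0, 1, 6, 12. Four points, with gaps of 1, 5 and 6 weeks.
- Partners: weeks 0, 1, 12. Three points, with gaps of 1 and 11 weeks.

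Even a first-order autoregression has three parameters (mean, autoregressive coefficient, variance). One patient supplies three successive pairs and one partner two, and no gap length occurs twice within a person. The information lies across people, which is what a repeated-measures model uses.

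**The case against.** Four points can be made for the plan.

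**The tests work.** A reader might infer that a linear model on a 0/1 outcome makes the p-values unreliable. The simulations do not support that: type I error stays near 0.05 and power matches logistic regression. Nor are the coefficients unreadable, since each is a difference in the probability of adherence per unit of predictor. This stands, and it confines the harm to fitted probabilities and to how r is read.

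**The day count may be meant.** Section 2.9 ties the dichotomy to the primary aim, and a 0-7 count exists. For the MAI sentence, which says only adherence at 12 weeks, this is possible. For IPQ-S it conflicts with (non)adherence, and the Discussion calls adherence outcomes dichotomous. At best it is an ambiguity to resolve.

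**Multiple regression need not be linear.** Correct. One could infer that the six-factor model is also wrong, but its type is not stated. If it were linear, with six predictors at an assumed log-odds ratio of 0.5 per SD, about 5% to 17% of fitted values would fall outside 0-1. That range should not be attached to the IPQ-S and MAI analyses, for which the document does not specify such a model.

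**The time-series aim is descriptive.** The text speaks of presenting change, and the Discussion of a tendency. So it goes too far to say that nothing can be done: means by visit can be shown. The lack of a between-arm comparison is no fault either, as the article states no such objective for illness beliefs and both arms receive that treatment. A formal time-series model remains unsuitable.

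**Conclusion.** The mismatch is real and rests on what Section 2.9 states. Pearson's r and linear regression are assigned to an outcome that the protocol calls dichotomous, and a time-series analysis to three or four unequally spaced measurements per person.

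Its size is moderate. Inference is not distorted to any degree that matters. The cost is impossible fitted probabilities (in 10-47% of simulated trials at slope 0.5 and 83-98% at slope 1.0, though only 0.1-6.5% of fitted values on average), an r whose ceiling shifts from 0.80 to 0.58 with the adherence rate, and no stated model for repeated illness-belief scores. These figures depend on the assumed rates and slopes, one normal predictor and N = 142.

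The primary analysis is untouched, because the chi-square test suits a binary outcome; so does the planned chi-square comparison by perceived social support. This is a should-fix.

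**What to change.** In Section 2.9:

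1. For IPQ-S and MAI against binary adherence, replace Pearson's r and linear regression with logistic regression, reporting odds ratios with 95% confidence intervals. Alternatively, state that the 0-7 day count is the outcome and name a model suited to it.
2. State that the multiple regression on age, gender, education, CIRS, VAS and QBPDS is logistic if adherence is binary.
3. Replace the time-series analysis with a linear mixed model (or GEE) with time as a categorical factor, fitted separately for patients and partners.

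Treatment arm in every model and arm-by-time terms are optional and are not needed to cure the mismatch.

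The cost is wording only: no new data, no change to sample size or significance level, and the models are available in the SPSS version already named.
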